# Supervised Home-Based Exercise Prehabilitation in Unfit Patients Scheduled for Pancreatic Surgery: Protocol for a Multicenter Feasibility Study

**DOI:** 10.2196/46526

**Published:** 2023-09-07

**Keywords:** preoperative care, prehabilitation, preoperative training, high-intensity interval training, pancreatic resection, cardiorespiratory fitness

## Abstract

**Background:**

Morbidity rates in pancreatic surgery are high, and frail patients with low aerobic capacity are especially at risk of complications and require prophylactic interventions. Previous studies of small patient cohorts receiving intra-abdominal surgery have shown that an exercise prehabilitation program increases aerobic capacity, leading to better treatment outcomes.

**Objective:**

In this study, we aim to assess the feasibility of a home-based exercise prehabilitation program in unfit patients scheduled for pancreatic surgery on a larger scale.

**Methods:**

In this multicenter study, adult patients scheduled for elective pancreatic surgery with a preoperative oxygen uptake (VO_2_) at the ventilatory anaerobic threshold ≤13 mL/kg/min or a VO_2_ at peak exercise ≤18 mL/kg/min will be recruited. A total of 30 patients will be included in the 4-week, home-based, partly supervised exercise prehabilitation program. The program comprises 25-minute high-intensity interval training on an advanced cycle ergometer 3 times a week. Training intensity will be based on steep ramp test performance (ie, a short-term maximal exercise test on a cycle ergometer), aiming to improve aerobic capacity. Twice a week, patients will perform functional task exercises to improve muscle function and functional mobility. A steep ramp test will be repeated weekly, and training intensity will be adjusted accordingly. Next to assessing the feasibility (participation rate, reasons for nonparticipation, adherence, dropout rate, reasons for dropout, adverse events, and patient and therapist appreciation) of this program, individual patients’ responses to prehabilitation on aerobic capacity, functional mobility, body composition, quality of life, and immune system factors will be evaluated.

**Results:**

Recruitment for this study began in January 2022 and is expected to be completed in the summer of 2023.

**Conclusions:**

Results of this study will provide important clinical and scientific knowledge on the feasibility of a partly supervised home-based exercise prehabilitation program in a vulnerable patient population. This might ease the path to implementing prehabilitation programs in unfit patients undergoing complex abdominal surgery, such as pancreatic surgery.

**Trial Registration:**

ClinicalTrials.gov NCT05496777; https://classic.clinicaltrials.gov/ct2/show/NCT05496777

**International Registered Report Identifier (IRRID):**

DERR1-10.2196/46526

## Introduction

The incidence of pancreatic malignancies is predicted to rise as the aging population grows [1]. The only curative treatment option remains pancreatic surgery, which is highly complex and known for its high postoperative morbidity [2]. Within this already vulnerable patient group, there are unfit patients with low aerobic fitness, translating into a limited reserve to withstand stress during surgery [3,4]. As a consequence, these patients are more prone to postoperative morbidity after pancreatic surgery [5,6]. To effectively identify unfit patients who are in need of preoperative intervention to reduce their perioperative risks, specific preoperative risk assessment is required. In the search for valid preoperative risk assessment diagnostics, preoperative aerobic fitness has been found to have a persistent relationship with postoperative outcomes in major elective intra-abdominal surgeries [5,7,8]. A cardiopulmonary exercise test (CPET), which determines 2 meaningful risk indicators, that is, the oxygen uptake (VO_2_) at the ventilatory anaerobic threshold (VAT) and VO_2_ at peak exercise (VO_2peak_), can be used to acquire an objective representation of a patient’s aerobic capacity [9].

Physical exercise training before surgery has been reported to effectively increase the aerobic capacity of patients scheduled for major abdominal surgery [10-17]. In the trial of Barberan-Garcia et al [18], high-risk patients scheduled for major abdominal surgery were subjected to a multimodal prehabilitation program consisting of (1) motivational interviewing, (2) a personalized program to promote daily physical activity, and (3) a supervised high-intensity endurance exercise training program. The mean duration of their program was 6 weeks, and it not only improved preoperative aerobic capacity, but also resulted in a 51% reduction in postoperative complications [18]. Regarding prehabilitation programs in pancreatic surgery, Ausania et al [14] subjected patients with a pancreatic or peripancreatic malignancy, regardless of their physical fitness, to a multimodal prehabilitation program consisting of 5 daily sessions of supervised high-intensity endurance training in the outpatient clinic. Furthermore, patients were trained to perform unsupervised home-based functional and breathing exercises, and nutritional support, as well as pancreatic exocrine insufficiency, was addressed [14]. Although the authors reported an improvement in physical fitness as determined by the 10-meter walk test, no differences in postoperative outcomes were observed [14]. However, since high-risk patients are hypothesized to benefit the most from exercise prehabilitation, adequate patient selection seems essential and greatly influences the effect of an exercise prehabilitation program on improving a patient’s aerobic capacity [11,12]. Another important factor influencing the feasibility and effect of a prehabilitation exercise program is the setting in which it takes place. Most reported prehabilitation programs have been carried out in an outpatient clinic. However, as pointed out by Ferreira et al [19], patients prefer a home-based prehabilitation program for reasons such as traveling issues or because a hospital- or community-based exercise program is regarded as too time-consuming. These perceived barriers will negatively influence a patient’s adherence to a physical exercise training program, likely resulting in a suboptimal training effect [19]. On the other hand, a possible disadvantage of unsupervised home-based exercise training could be a lack of adherence of the patient, lack of appropriate exercise intensity, and therefore lack of benefit [4]. It is therefore important to provide adequate supervision, preferably by an experienced physical therapist.

In exercise prehabilitation programs within a limited preoperative time window of 4 to 6 weeks, the most efficient training modality to increase aerobic capacity seems to be high-intensity interval training (HIIT) [17,20]. In a study by van Wijk et al [17], high-risk patients scheduled for liver or pancreatic surgery participated in a partly supervised home-based bimodal prehabilitation program consisting of HIIT and high-intensity endurance training combined with nutritional support. Their 4-week prehabilitation program was shown to be feasible and improved aerobic capacity by 17% as determined by performing a CPET pre- and postintervention.

Although several studies investigated the effect of exercise prehabilitation in major abdominal surgery, there is a large heterogeneity in patient selection and prehabilitation program setting, which notably influences its effectiveness and adequate interpretation of results. Therefore, the primary aim of this study is to determine the feasibility of a 4-week, home-based, partly supervised exercise prehabilitation program in unfit patients scheduled for pancreatic surgery. Secondary aims of the study are to evaluate the individual responses to the program on aerobic capacity, functional mobility, muscle strength, body composition, level of perceived fatigue, quality of life, and immune system factors.

## Methods

### Study Design

The described study is a multicenter feasibility study, and the study will have a pretest-posttest design. The latest version of the study protocol (version 7; May 2022) is presented in this manuscript. Protocol amendments will have to be approved by the Medical Research Ethics Committee of the Maastricht University Medical Center+ and Maastricht University (METC azM/UM).

### Eligibility Criteria

In order to be eligible to participate in this study, patients must meet all of the following criteria: (1) age 18 years or older, (2) planned for elective pancreatic surgery at Maastricht University Medical Center+ or at the University Medical Center Groningen, and (3) providing informed consent to participate. Patients are considered eligible (4) if they have a VO_2_ at the VAT ≤13 mL/kg/min or a VO_2peak_ ≤18 mL/kg/min. A patient who meets any of the following criteria will be excluded from participation in this study: (1) they require acute surgery, (2) they undergo surgery in another hospital, (3) they are not able to cycle on a cycle ergometer, (4) contraindications are identified for them to physical exercise training (eg, heart rhythm disturbances, ischemia of the heart muscle), (5) they are unable to cooperate during the testing procedures (eg, insufficient understanding of the Dutch language), and (6) no certified physical therapist is available in their living area.

### Recruitment

All patients eligible for pancreatic surgery will be identified at the multidisciplinary team meetings and evaluated by the surgeon at the outpatient clinic. During the outpatient clinic visit, patients will be given full details of the study, and after a few days, patients from the Maastricht University Medical Center+ will be contacted by telephone by a designated investigator to provide extensive information about the study. If patients are interested in participating in the study, a CPET will be performed to check whether the patient fulfills the inclusion criteria, after which an appointment will be planned to perform baseline assessments and to retrieve written informed consent. At the University Medical Center Groningen, all patients scheduled for pancreatic surgery perform a CPET as part of usual care. Based on the CPET results, patients will be asked to participate in this study and an appointment will be planned to perform the remaining baseline assessments and receive written informed consent.

### Interventions

#### Preoperative Home-Based Physical Exercise Training Program

Participating patients will engage in a home-based, partly supervised exercise prehabilitation program before elective pancreatic surgery. The physical exercise training program will consist of HIIT on an advanced cycle ergometer that is placed at the patient’s home (Lode Corival Home+, Lode BV; see Figure 1), with the goal to improve the patient’s preoperative aerobic fitness. A certified community physical therapist in the living area of the patient will be asked to partly supervise the physical exercise training program. The community physical therapist will receive verbal and written instructions on the use of the cycle ergometer and the goals and content of the program.


**Figure 1 figure1:**
[figure not shown]
The Lode Corival Home+ cycle ergometer used in this study.

**Table 1 table1:** High-intensity interval training structure.

Exercise phase		Exercise intensity	Pedaling frequency (rotations/min)	
Warm-up (3 min)		20 W	40-80	
**Interval training (21 min)**				
	Work interval intensity (14 repetitions)	30 sec at 60% of WR_peak_^a^ of the steep ramp test	60-100	
	Rest interval intensity (14 repetitions)	60 sec at 20 W	40-60	
Cooldown (1 min^b^)		20 W	40-80	

^a^WR_peak_: work rate at peak exercise.

^b^Duration of cooldown can be extended when preferred.

**Figure 2 figure2:**
[figure not shown]
(a) Example of modified steep ramp test performance. (b) Results of a consecutive high-intensity interval training session at 60% of steep ramp test WR_peak_. HR: heart rate; WR: work rate; WR_peak_: work rate at peak exercise.

#### Functional Task Exercises

Next to HIIT on the cycle ergometer, patients will be instructed to carry out functional task exercises 2 times a week on training days at which the HIIT session is not preceded by an SRT, thereby practicing activities relevant to the patient (eg, elastic band exercises, stair-climbing, brisk walking) [24]. An overview of the structure of the overall training program can be found in Table 2. The patient will be instructed to perform at least 3 repetitions of about 30 seconds of different functional task exercises with 30 seconds of rest in between. The functional task exercises will be chosen individually, consisting of activities relevant to the patient, and the intensity and complexity of exercises will be individually reviewed weekly by the physical therapist. Patients will be instructed to perform as many repetitions as intensely as possible, but at least three per functional task exercises. Next to an increasing exercise intensity or frequency, functional task exercises can also progress in difficulty in terms of making exercises more complex and by adding variation.

**Table 2 table2:** Overall training program structure (weeks 1-4).

Training session 1 (Monday or Tuesday)		Training session 2 (Wednesday or Thursday)			Training session 3 (Friday or Saturday)	
Workout	Duration	Workout	Duration	Workout		Duration
SRT^a^	4-7 minutes	HIIT^b^	25 minutes	HIIT		25 minutes
HIIT	25 minutes	Functional task exercises	15 minutes	Functional task exercises		15 minutes

^a^SRT: steep ramp test.

^b^HIIT: high-intensity interval training.

### Usual Care

As part of usual care, all patients are screened at baseline for risk factors associated with postoperative complications and are treated accordingly. This includes screening for nutritional deficits, mental resilience, anemia, iron deficiency, hyperglycemia, and substance abuse (eg, smoking, alcohol consumption). In both participating centers, patients are screened by a trained dietitian as part of usual care. Patients at risk of malnutrition will receive additional nutritional support. When patients are in need of additional support in any of the other areas, such as psychological support or intervention for smoking cessation, this will also be implemented as a standard of care in both centers.

### Measurements

Before, during, and after the preoperative home-based physical exercise training program, several outcome measurements will be obtained (Table 3).

**Table 3 table3:** Schedule of enrollment, intervention, and assessments.

			Preintervention	Home-based exercise prehabilitation					Postintervention		Follow-up (30 days postoperatively)
				Week 1	Week 2	Week 3	Week 4				
**Enrollment**											
		Eligibility screening	✓								
		Informed consent	✓								
**Intervention**											
		Home-based exercise prehabilitation		✓	✓	✓	✓				
**Assessments**											
		Baseline characteristics	✓								
		Feasibility	✓	✓	✓	✓	✓	✓			
	**Aerobic capacity**										
		CPET^a^	✓					✓			
		SRT^b^		✓	✓	✓	✓				
	**Muscle strength**										
		Handgrip strength	✓					✓			
	**Body composition**										
		Anthropometry	✓	✓	✓	✓	✓	✓			
		L3^c^ index	✓					✓			
	**Functional mobility**										
		30-second chair-stand test	✓	✓	✓	✓	✓	✓			
		2-minute walk test	✓					✓			
	Immunological phenotyping		✓					✓			
	**Questionnaires**										
		MFI^d^	✓					✓			
		EORTC QLQ-C30^e^	✓					✓			
		SARC-F^f^	✓					✓			
		Program appreciation^g^						✓			
	**Postoperative outcomes**										
		Surgical complications								✓	
		Length of hospital stay								✓	
		30-day readmission								✓	

^a^CPET: cardiopulmonary exercise test.

^b^SRT: steep ramp test.

^c^L3: third lumbar vertebra.

^d^MFI: Multidimensional Fatigue Index.

^e^EORTC QLQ-C30: European Organization for Research and Treatment of Cancer Quality-of-life Questionnaire Core 30.

^f^SARC-F: strength, assistance with walking, rising from a chair, climbing stairs, and falls.

^g^Patient and community physical therapist appreciation.

#### Program Feasibility

Feasibility will be determined by (1) monitoring the participation rate of this study as well as reasons for nonparticipation. Reasons for nonparticipation will be asked for during a short interview with the coordinating investigator or treating surgeon. Furthermore, feasibility will be determined by (2) evaluating adherence and fidelity of patients to the physical exercise training program as objectively recorded by the cycle ergometer, which provides insight into training session content (eg, frequency, intensity, duration, premature termination of a training session), (3) dropout rate and reasons for dropout, (4) number and severity of adverse events, and (5) patient and therapist appreciation after completing the program by filling out a short questionnaire based on a previous study [25]. If a patient drops out before the end of the training program, the reasons will be investigated through a short interview with the coordinating investigator.

#### Aerobic Capacity CPET

For all patients, a preintervention CPET will be performed by a clinical exercise physiologist (Maastricht University Medical Center) or sports physician (University Medical Center Groningen) to assess baseline aerobic capacity, which will be used to make a selection of eligible unfit patients and thereupon invite them to participate in the study (VO_2_ at the VAT ≤13 mL/kg/min or VO_2peak_ ≤18 mL/kg/min). After completion of the program, a postintervention CPET will be performed. The outcome thereof will be used to assess the effectiveness of the home-based physical exercise training program to improve aerobic capacity.

The CPET will be executed under controlled conditions using a calibrated electronically braked cycle ergometer in an upright position; the Lode Corival CPET (Lode BV) will be used at Maastricht University Medical Center and the Lode Excalibur Sport (Lode BV) will be used at the University Medical Center Groningen. Patients will be fitted with a 12-lead electrocardiogram to rule out strain-related cardiac ischemia, arrhythmias, and other contraindications for intense physical exercise training during the consecutive exercise program. During the test, patients will breathe through a face mask connected to a metabolic cart; the Vyntus CPX (Vyaire Medical) will be used at the Maastricht University Medical Center and the Quark CPET (Cosmed) will be used at the University Medical Center Groningen for measurements of breath-by-breath VO_2_, minute ventilation, and carbon dioxide production throughout the CPET. Finally, heart rate and blood pressure will be monitored, and peripheral oxygen saturation will be measured at the index finger. After 2 minutes of rest measurements, the patient is asked to start cycling. The first 2 minutes consist of unloaded cycling. Thereafter, the WR will be linearly incremented with a 5, 10, 15, or 20 W/min ramp protocol (depending on the patient’s self-reported physical fitness) to ensure a test duration between 8 and 12 minutes. Patients will be instructed to maintain a pedaling frequency of around 80 revolutions/min. The test effort will be considered maximal when the patient shows objective signs (ie, heart rate at peak exercise >95% of predicted or a respiratory exchange ratio at peak exercise >1.10) or subjective signs (eg, unsteady biking, sweating, clear unwillingness to continue exercising despite strong encouragement) of maximal effort. CPET interpretation will be performed according to international guidelines by an experienced sports physician or medical physiologist [26]. The last 30 seconds before termination of the test will be used to calculate absolute values at peak exercise. Peak heart rate is the highest heart rate achieved throughout the test. The VAT is described as the point at which the partial end-tidal oxygen tension and the ventilatory equivalent for oxygen reached a minimum and thereafter began to rise in a consistent manner, corresponding with an unchanged ventilatory equivalent for partial end-tidal carbon dioxide tension and carbon dioxide [26]. If this method provides unreliable results, the V-slope method will be applied instead [27].

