### Data Analysis

#### Sample Size Calculation

This study will specifically evaluate the feasibility of a home-based, partly supervised prehabilitation program in unfit patients undergoing elective pancreatic surgery. Thus, the study has a clear explorative character and will analyze individual responses to the program. Based on the number of patients undergoing elective pancreatic surgery annually and the relatively short study period (<1 year), 15 patients who are willing to participate in the study will be included per hospital, resulting in a total of 30 patients. Results of this exploratory study will provide information on how to proceed in subsequent effect studies. Furthermore, results can be used to optimize the home-based prehabilitation program in the future.

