#### Statistical Analysis

The R software package (R Foundation for Statistical Computing) will be used for statistical analysis. Collected data on patient characteristics will be presented in tables. Continuous variables will be displayed as mean (SD), while categorical variables will be presented as number (n) and percentage (%). Descriptive statistics will be used to answer the primary study parameter of feasibility. As previously described, feasibility will be presented in tables and based on participation rate (n, %), reasons for nonparticipation (n, %, text), adherence to the program (%), dropout rates (%), reasons for dropout (n, %, text), adverse events (n, %, text), patient motivation (scale 0-10), and appreciation (text). The secondary aim is to evaluate the patients’ responses over time in terms of aerobic capacity, muscle function, functional mobility, body composition, perceived fatigue, quality of life, and immune system function. Individual response profiles will be graphically depicted and presented in tables. A repeated measurements analysis will be used to analyze changes over time in continuous variables. *P* values <.05 will be considered statistically significant.

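### The post-training CPET is meant to assess effectiveness, but with no comparison group and a baseline that is also the selection test it can only describe change

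*Protocol article*

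**What the plan says.** The Study Design section states that "the study will have a pretest-posttest design"; no comparison group is described.

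Under Eligibility Criteria, patients qualify "if they have a VO_2_ at the VAT ≤13 mL/kg/min or a VO_2peak_ ≤18 mL/kg/min". The Aerobic Capacity CPET section says that the preintervention CPET is done "to assess baseline aerobic capacity, which will be used to make a selection of eligible unfit patients", so one test does both jobs. Table 3 shows one CPET before the program and one after. At Groningen the selection CPET is the usual-care test, and afterwards "an appointment will be planned to perform the remaining baseline assessments", which leaves no second CPET before training.

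On the post-training test the same section says: "The outcome thereof will be used to assess the effectiveness of the home-based physical exercise training program to improve aerobic capacity". Under Statistical Analysis, changes in continuous variables get a repeated measurements analysis, and P "values <.05 will be considered statistically significant". Individual response profiles are to be shown in graphs and tables. The Sample Size Calculation section calls the study exploratory, says that it "will analyze individual responses to the program", and expects its results to guide later effect studies.

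The limitations in the Discussion name partial supervision and the exercise-only program. They mention neither the missing control group nor selection on the baseline test.

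**The concern.** Patients are admitted because a noisy measurement fell below a cut-off. Some were below it partly by chance, and their next test will on average be higher whether or not they trained. Without a comparison group this rise cannot be told apart from a training effect. Familiarization with the test, concurrent usual care and the course of the disease cannot be separated either.

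For individual patients, a single difference between two tests contains the error of both.

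Two conclusions are at stake: a statement that the program improves aerobic capacity, and a reading of particular patients as having responded. An inflated mean change could also be carried into the planning of a later effect study. The primary outcome, feasibility, is descriptive and is not affected.

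**Working it through.** **The plan's own figure.** 15 patients per hospital × 2 hospitals = 30, as stated. It is a pragmatic number with no effect size, SD or power, so there is no power figure to reproduce.

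**Inputs from the article.** The either/or cut-off (VAT ≤13 or VO2peak ≤18 mL/kg/min), n = 30, alpha .05 (sidedness not stated; two-sided assumed), one CPET before and one after. Cited group gains are 10% (colorectal surgery) and 17.8% and 17.2% (liver or pancreatic resection).

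**Assumed, because the article gives no figures.** Screened-population means and SDs as in the table; correlation of true VAT and VO2peak 0.8; correlation of their errors within one test 0.5; test-retest CV 5–10%.

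**Group change with zero training effect.** Two million screened patients were simulated, selected by the protocol's rule on test 1, and tested again. A paired t-test was applied in samples of 30; with two time points this is what a simple repeated measurements analysis amounts to. The error SD is CV × population mean.

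| Screened mean (SD), VO2peak; VAT | CV | Spurious gain, VO2peak / VAT | P<.05, VO2peak / VAT | Patients with gain ≥10%, VO2peak / VAT |
|---|---|---|---|---|
| 18 (4.5); 12 (2.5) | 5% | 0.4% / 0.6% | 5.9% / 6.7% | 13% / 13% |
| 18 (4.5); 12 (2.5) | 10% | 1.6% / 2.1% | 8.2% / 10.8% | 31% / 31% |
| 20 (5); 13 (3) | 5% | 0.6% / 0.8% | 6.6% / 8.2% | 15% / 15% |
| 20 (5); 13 (3) | 10% | 2.2% / 3.0% | 10.5% / 15.6% | 33% / 34% |
| 22 (5); 14 (3) | 5% | 0.8% / 1.2% | 7.7% / 11.1% | 16% / 17% |
| 22 (5); 14 (3) | 10% | 3.1% / 4.4% | 15.6% / 26.6% | 35% / 38% |

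The ends of these ranges depend on the assumptions. Letting the error scale with the patient's own true value, on the same grid, gives gains of 0.5–4.1%, false positives of 6–29%, and 10–33% of patients with a gain of at least 10%. A further null simulation over the same CV range, with its own assumed means and SDs, gave:
- gains of 0.5–4.3% (VAT) and 0.4–2.8% (VO2peak);
- false positives of 6–32% (VAT) and 6–17% (VO2peak);
- 10–34% of patients with a gain of at least 10%.

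**Is selection on the baseline the cause?** Keep the selection on test 1 but take a separate second pre-training test as baseline. The mean change becomes 0.0% and the false-positive rate about 5% (4.6–5.3%). So the group bias comes from using the selection test as baseline. Even then, 12–29% of patients show a gain of at least 10% from noise alone.

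**Limit for one patient.** 95% limit = 1.96 × √2 × CV. At CV 5%: 1.96 × 1.414 × 0.05 = 13.9%. At CV 10%: 27.7%.

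**Precision of the group mean.** SE = CV × √2 / √30 = 1.29% to 2.58%. Times t(29) = 2.045, the 95% half-width is 2.6% to 5.3%. This counts test error only, with all 30 patients completing and no variation in true response.

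**Scaling by body mass.** At unchanged VO2 in mL/min, a 3% weight loss reads as 1/0.97 − 1 = 3.1% gain in mL/kg/min. Weight gain does the reverse.

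**The case against.** The strongest reply is that this is an exploratory feasibility study with a descriptive primary outcome and a deliberately loose cut-off, so the bias is small. Much of that stands. In the tabulated scenarios a null result stays non-significant for a given variable in 73–94% of trials, and test noise does not bias a group mean. But the article does not stop at description: it names effectiveness as what the post-test is for. No analysis plan can supply the missing comparison group, so this is a stated inference that the design cannot carry, not a detail left to another document.

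Several stronger readings are tempting, and the documents do not support them:

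- *Any gain found will be artefact.* A 10% group gain lies well outside both the spurious gain and the 2.6–5.3% half-width. The 14–28% limit applies to one patient and must not be set against group gains.
- *The article will label responders by P value.* It plans only graphs and tables of individual profiles; the P rule concerns change over time.
- *The P<.05 rule must go, or the outcomes must be ranked.* In an exploratory study that is a preference. Labelling the P values is enough.
- *The weekly steep ramp test slope is the better individual measure.* With equal test error s, the slope over four weekly tests has SD s/√5 = 0.447s per week. A pre-post difference over four weeks has √2·s/4 = 0.354s per week. The slope is noisier, and it is uncontrolled too.
- *Groningen data can correct the bias.* There "all patients scheduled for pancreatic surgery perform a CPET as part of usual care", but nothing shows that nonparticipants' values are study data, and the two centers use different ergometers and metabolic carts.
- *Nutritional support inflates the result.* If it raised weight, mL/kg/min would fall.

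**Conclusion.** The concern holds in a limited form. The article's effectiveness wording, together with testing at P<.05, claims more than an uncontrolled pre-post change from a selection-test baseline can show.

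The direction of the group bias is certain: upward, with a false-positive rate above 5%. Its size, roughly 0.4–4% spurious gain and 6–32% false positives per variable, rests wholly on assumed means, SDs and a CV of 5–10%. A reader might infer that regression to the mean could account for gains like the cited 10–18%; under these assumptions it could not on its own.

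The point is strongest for individual response. Roughly 10–34% of patients (up to 38% if the error is constant in mL/kg/min) would appear to gain at least 10% with no true change, and a change within about 14–28% cannot be told from test-retest variation in one patient.

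The change should be made, but it concerns secondary outcomes only.

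**What to change.** 1. In the Aerobic Capacity CPET section, replace the effectiveness sentence by one saying that the postintervention CPET will describe the within-patient change in aerobic capacity after the program. Report the mean change with a 95% CI, and label P values for secondary outcomes as exploratory.
2. In the Discussion, add two limitations: no control group, and regression to the mean from selection on the baseline CPET. State that the observed change must not be used uncorrected as the effect size of a later effect study.
3. Draw a test-retest band on the individual response plots, state the CV assumed for it, and do not interpret changes inside it as individual response.
4. Report VO2 in mL/min beside mL/kg/min.

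The cost is wording and analysis only: no new visits or tests, and body mass is already measured before, weekly during and after the program. The downside is that fewer results can be read as evidence of effect.

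### A CPET can be classed as maximal on subjective signs alone, so harder effort at the second test can read as a VO2peak gain in the individual response profiles

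*Protocol article*

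**What the plan says.** The section Aerobic Capacity CPET sets the effort rule in one sentence with two limbs. The first reads "The test effort will be considered maximal when the patient shows objective signs", specified as a peak heart rate above 95% of predicted or a peak RER above 1.10. The second, joined by a plain *or*, is "subjective signs (eg, unsteady biking, sweating, clear unwillingness to continue exercising despite strong encouragement) of maximal effort". The list in the second limb is open.

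The peak value is then fixed without reference to why the test ended: "The last 30 seconds before termination of the test will be used to calculate absolute values at peak exercise".

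The same section gives the use of the post-program test: "The outcome thereof will be used to assess the effectiveness of the home-based physical exercise training program to improve aerobic capacity". Study Design describes a pretest-posttest study, with no comparison group. Statistical Analysis plans individual response profiles and a repeated measurements analysis of change, with significance at P<.05.

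Under Eligibility Criteria, a patient enters with VO2 at the VAT of at most 13 mL/kg/min or VO2peak of at most 18 mL/kg/min. No effort condition is attached to either limb.

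**The concern.** VO2peak depends on how far the patient pushes; a test that ends early gives a lower value. A rule that accepts subjective signs on their own lets such a test stand as maximal even when both objective criteria fail.

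The error need not be the same at both tests. Between them, patients do a maximal steep ramp test each week with strong verbal encouragement (sections on the training program and on the modified SRT). That is practice at cycling to exhaustion, so a shift towards fuller effort at the second CPET is plausible, although the article does not measure it. With no control group, such a shift looks the same as a training effect on VO2peak. What is at stake is the reading of each patient's VO2peak change and, for a narrow group, whether the patient was unfit by the study's own threshold.

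**Working it through.** **The plan's own figure.** The sample size is 15 patients × 2 hospitals = 30, which reproduces. It rests on feasibility, and nothing below depends on a power calculation.

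**Inputs from the article.** VO2peak limit 18 and VAT limit 13 mL/kg/min (Eligibility Criteria); gains cited in the Discussion from earlier studies: 10% (colorectal surgery) and 17.2% in VO2peak (liver or pancreatic resection).

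**Assumed input.** The shortfall *s* of a baseline VO2peak below the true peak. The article gives no value; the range 5% to 20% is used. Effort at the second test is taken as full and true fitness as unchanged.

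**Formulas.** Measured baseline = true peak × (1 − s). Apparent gain = 1/(1 − s) − 1. Highest true peak that still meets the VO2peak limit = 18/(1 − s).

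| Shortfall s (assumed) | Apparent gain | Highest true peak admitted (mL/kg/min) |
|---|---|---|
| 5% | 1/0.95 − 1 = 5.3% | 18/0.95 = 18.95 |
| 10% | 1/0.90 − 1 = 11.1% | 18/0.90 = 20.0 |
| 15% | 1/0.85 − 1 = 17.6% | 18/0.85 = 21.18 |
| 20% | 1/0.80 − 1 = 25.0% | 18/0.80 = 22.5 |

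One patient: true peak 20, baseline stopped 15% short. Measured 20 × 0.85 = 17.0; second test 20; apparent gain 20/17.0 − 1 = 17.6%.

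**Against the cited gains.** The shortfall that alone would imitate a gain *g* is 1 − 1/(1 + g). For 10% it is 1 − 1/1.10 = 9.1%; for 17.2% it is 1 − 1/1.172 = 14.7%.

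**Group mean.** If a fraction *f* of patients fall short by *s*, the mean false gain is about f × [1/(1 − s) − 1]. With f = 10% and s = 5% it is 0.1 × 5.3% = 0.5%; with f = 30% and s = 15% it is 0.3 × 17.6% = 5.3%. Both *f* and *s* are assumed. The exposure is therefore larger for single profiles than for the mean.

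**Entry.** A low VO2peak changes admission only if the VAT limb would not have admitted the patient anyway, that is, if VO2 at the VAT exceeds 13. For a true peak of 20 that means a VAT above 13/20 = 65% of peak; for 22.5 it means above 13/22.5 = 58%. The article does not say how common this is.

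**The case against.** **The reader is competent and the text speaks of signs of maximal effort.** Tests are interpreted by experts: "CPET interpretation will be performed according to international guidelines by an experienced sports physician or medical physiologist". The examples include unwillingness to go on despite strong encouragement. A reader might infer that sweating alone makes nearly every test maximal. That is the most literal reading, and the article does not show that it would be applied so. What stands is narrower: the written rule does not hold the reader to any objective sign.

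**Eligibility does not hang on the effort label.** This is correct. The entry criteria use oxygen uptake values with no effort condition, so a short test could admit a patient even under a strict rule. The entry effect is limited to patients who qualify on VO2peak alone.

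**Ramp and VAT method.** A reader might infer that both are chosen afresh for each test, because "the WR will be linearly incremented with a 5, 10, 15, or 20 W/min ramp protocol" is tied to self-reported fitness, and because of the sentence "If this method provides unreliable results, the V-slope method will be applied instead". The article does not say so. It describes the CPET once and is silent on whether settings are kept for the second test, which the full protocol may fix. V-slope is a fallback, not a free choice, and CPET peak work rate is not a named outcome. No fault is claimed here.

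**Training and effort can be told apart with data at hand.** This largely stands. Heart rate, the gas exchange from which RER follows, and VO2 at the VAT are measured at both tests. That makes the point cheap to repair, but the article does not say that these data will be used to qualify VO2peak.

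**The outcome is secondary and the study exploratory.** This is true, and it limits the weight of the point.

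**Conclusion.** The point holds in a limited form. The effort rule, as written, allows a VO2peak without any objective sign of maximal effort to be accepted as maximal and used as the baseline for change. Under an assumed baseline shortfall of 5% to 20%, with full effort later and no true change, the apparent individual gain is 5% to 25%, which spans the 10% and 17.2% gains that the article cites. The mean false gain would be much smaller, about 0.5% to 5.3% if 10% to 30% of patients fell 5% to 15% short. These sizes rest wholly on the assumed shortfall and on effort rising between tests; neither is shown in the article.

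The reach is the VO2peak part of a secondary outcome, chiefly the individual profiles. Entry is touched only where VO2peak is at most 18 and VO2 at the VAT is above 13. The feasibility outcome is largely unaffected. No responder cut-off is defined, so the issue is one of measured change, not of responder counts. It is worth correcting because the correction is cheap, not because it threatens the study's main aim.

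**What to change.** - Class a VO2peak as maximal only when one of the two objective signs already named is met; flag tests with subjective signs only.
- Keep all patients in the main analysis of VO2peak change. Add a sensitivity analysis limited to pairs with an objective sign at both tests.
- Show peak RER and peak heart rate at both tests beside each individual profile.
- Make VO2 at the VAT the leading aerobic response, since it does not need maximal effort.
- Report how many patients entered on VO2peak alone from a test without an objective sign.
- Where feasible, read both VATs of a patient by the same method and without knowledge of test order.

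The cost is a little more analysis. The inputs are already recorded, so most of this can still be done if recruitment has ended. The sensitivity set will be smaller than the at most 30 available pairs and may leave out the frailest patients. It also selects partly on a post-intervention result, which is why it should stand beside the full analysis and not replace it.
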